#### Objective 2b: Examine the Effectiveness of SSBC

All clients will complete in-person measurements (weight and waist circumference) at baseline, 12-, and 24-month post program. At locations with an appropriate space (ie, walking track), cardiorespiratory fitness will also be assessed via a 6-minute walk test [79]. In addition, all clients will complete surveys at baseline, session 6, 12, and 24 months post program via REDCap (Research Electronic Data Capture). Surveys will assess self-reported T2D status (12- and 24-months only [80,81]), moderate-to-vigorous PA, dietary intake, and health-related quality of life (EQ-5D-5L) [82]. Table 3 outlines the measures that will be used in the evaluation of SSBC effectiveness. Using an equity-focused lens, a prospective cohort subsample of clients (n=1285) will be followed across 24 months to evaluate the differential impact of SSBC on T2D status, assessed by change in HbA_1c_, in addition to self-reported T2D status. All effectiveness outcomes will be analyzed using descriptive statistics. Hierarchical multivariable regression models will be used to assess the impact of SSBC on effectiveness outcomes, adjusting for potential confounders and accounting for within-subject and within-site clustering. Covariates (ie, sex, gender, and ethnicity) will be included to adjust for within-subject and within-site correlations. A sensitivity analysis using missing data imputation will be conducted to evaluate the potential impact of nonadherence on study outcomes. Data will be disaggregated to examine differences in effectiveness by ethnicity, socioeconomic status, municipality, sex, and gender within and between sites. For the subsample, a multilevel binary logistic regression will be used to examine differences in sociodemographic factors between those who do and do not experience a clinically significant reduction in HbA_1c_ at 24 months.

**Table 3 table3:** Overview of effectiveness measures and associated time points.

		Eligibility	Baseline measurement	Postprogram measurement	Follow-up measurements	
Measure		Online intake survey	Baseline on session 1	After session 6	12-month follow-up	24-month follow-up
Age		✓				
Current T2D^a^ diagnosis		✓				
Prediabetes diagnosis or ADA^b^ diabetes risk score		✓				

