To date, no community-based nationwide DPP has been implemented across Canada. To make a measurable impact on T2D prevention at a population level, potent evidence-based interventions must be implemented effectively at scale. Nationwide uptake of DPPs is hindered by the absence of evidence-informed implementation plans tailored to local contexts [38] and the examination of individual- and between-delivery site differences to understand the impact of context on implementation. Site contextual differences are common, as each community has unique challenges and opportunities that impact implementation, and remain an understudied paradox of implementation efforts [39]. Additionally, equity-based contextual factors, including access and cultural relevance for populations traditionally underserved and racialized against, are pivotal considerations for implementation scale-up [40,41]. It is imperative to disaggregate multisite data and understand how community-, organization-, provider-, and client-level factors contribute to implementation outcomes when organizations deliver the same program in different contexts [41,42]. Implementation studies with a focus on context, and in particular health equity, are needed to compare within and between-site implementation outcomes and determinants [41]. Understanding these contextual factors is also key for identifying methods (implementation strategies) required to enhance the implementation and scale-up of DPPs [43].

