### Intervention

SSBC aims to empower individuals with prediabetes to make long-lasting diet and PA changes. Trained SSBC coaches meet with clients for 6 one-on-one sessions focused on PA, reducing intake of added sugar, improving carbohydrate choices, and preventing relapse, with each session followed by supervised aerobic exercise. Coaches use a motivational interviewing-informed approach to bolster client autonomy. The core components of the SSBC program can be found in Textbox 1, and specific behavior change techniques are published elsewhere [62].

The core components of Small Steps for Big Changes.

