Quantitatively, organizational readiness will be assessed at baseline [70] through surveys with site leads and coaches. Implementer satisfaction with the program will be captured using the Behavioral Interventionist Satisfaction Survey [71] and the Intervention Acceptability, Appropriateness, and Feasibility [72] measures during the delivery process. Client receptivity and satisfaction will be assessed quantitatively using the 8-item Theoretical Framework for Acceptability [73], a 7-item overall program satisfaction measure, and the 1-item net promoter score [74]. In addition, client interviews will be conducted with a purposive subsample (2-3 clients per site) post-SSBC completion to assess client satisfaction and acceptability. Program costs will be captured through monthly invoices and annual reports from sites.

Quantitative data from adoption, reach, dose, fidelity, program cost, and client and coach receptivity measures will be analyzed descriptively. Client demographics will be used to assess representativeness relative to people with prediabetes across Canada. SSBC program sessions will be audio-recorded using tablets with data saved on the University of British Columbia’s secure data research network in real-time; 2 program sessions per year from each coach will be randomly sampled and coded using an abbreviated version of the validated Motivational Interviewing Competency Assessment [75]. Motivational Interviewing Competency Assessment scores will be used to assess coach counseling fidelity, as done previously [57]. All implementation strategies used will be identified and classified according to definitions from the Expert Recommendations for Implementing Change project [76].

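### The effectiveness models name client and site clustering but no coach level, so part of any coach variation would appear as between-site variation and site comparisons would look too certain

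*Protocol article*

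**What the plan says.** Under Objective 2b, the protocol article states that the hierarchical multivariable models will assess the effectiveness outcomes while "accounting for within-subject and within-site clustering". It then names the covariates: "Covariates (ie, sex, gender, and ethnicity) will be included to adjust for within-subject and within-site correlations". No coach variable appears in either place. The same section plans a comparison across places: "Data will be disaggregated to examine differences in effectiveness by ethnicity, socioeconomic status, municipality, sex, and gender within and between sites". For the HbA1c subsample, "a multilevel binary logistic regression will be used to examine differences in sociodemographic factors"; the levels of that model are not named.

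The Intervention section makes the coach the unit of delivery: "Trained SSBC coaches meet with clients for 6 one-on-one sessions". One-on-one delivery is also listed among the core components in Textbox 1. Under Objective 2a, two coaches at each site are to be interviewed, so more than one coach per site is expected. Counseling skill is scored coach by coach: "2 program sessions per year from each coach will be randomly sampled and coded". The analysis stated for fidelity is descriptive: "Quantitative data from adoption, reach, dose, fidelity, program cost, and client and coach receptivity measures will be analyzed descriptively".

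The article does not state how many coaches a site will have, whether a client keeps one coach for all six sessions, or any ICC.

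**The concern.** Clients sit within coaches and coaches within sites. The stated model has the first and last of these levels and skips the middle one. Coaches are peers with no required counseling background, and the study scores their competency individually, so it expects them to differ. If they do, two clients of the same coach resemble each other more than two clients at the same site with different coaches.

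A model without a coach level has to place that resemblance elsewhere. Some goes to site, where it reads as site context. The rest goes to the client residual. What is at stake is the comparison of effectiveness between sites and municipalities: a site with a few unusually effective coaches could be read as a site whose setting works better, with a standard error that makes the difference look firmer than it is.

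**Working it through.** The article gives no ICC, standard deviation or power calculation for this question, so there is no stated figure to reproduce. The check asks where coach variance goes when coach is left out.

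**Inputs from the article.** 44 planned sites (Organization Implementation Sites) and an HbA1c subsample of 1285 (Objective 2b): 1285/44 = 29.2, or about 29 clients per site.

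**Assumptions.** J coaches per site, from 1 to 8; coach ICC of 0.01 to 0.10; balanced numbers; each client with one coach; one change value per client. Total variance is set to 1 and true site variance to 0. The coach variance then equals the ICC, and the client variance is 1 − ICC.

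**Step 1: share of coach variance that moves to site.** With n = 29/J clients per coach:

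- expected between-site mean square: MSB = (1 − ICC) + n × ICC
- expected within-site mean square, coach ignored: MSW = (1 − ICC) + n(J − 1) × ICC/(Jn − 1)
- apparent site variance: (MSB − MSW)/(Jn) = ICC × (n − 1)/(Jn − 1)

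The share is therefore (n − 1)/(Jn − 1), close to 1/J:

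- J = 1: 28/28 = 100%
- J = 2: 13.5/28 = 48%
- J = 3: 8.67/28 = 31%
- J = 4: 6.25/28 = 22%
- J = 6: 3.83/28 = 14%

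The remainder goes to the client residual.

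**Step 2: standard error for comparing sites.** The understatement factor is √(MSB/MSW). At ICC 0.05:

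- J = 2: MSB = 0.95 + 14.5 × 0.05 = 1.675; MSW = 0.95 + 14.5 × 0.05/28 = 0.976; √1.716 = 1.31
- J = 4: MSB = 0.95 + 7.25 × 0.05 = 1.3125; MSW = 0.95 + 7.25 × 3 × 0.05/28 = 0.989; √1.327 = 1.15

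MSB grows with n while MSW barely changes, so outcomes measured on more clients per site than the subsample would show a larger factor.

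**Step 3: how often a 5% test of site differences would reject with no true site variance.** Simulation, 44 sites, about 29 to 30 clients per site, coach ignored:

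| Coaches per site | ICC 0.05 | ICC 0.02 |
|---|---|---|
| 2 | 82% | 33% |
| 3 | 57% | 21% |
| 4 | 38% | 15% |
| 6 | 23% | 11% |
| 8 | 17% | 9% |

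At ICC 0.01 the rates are 16%, 9% and 7% with 2, 4 and 6 coaches. At ICC 0.10 they are 99%, 92% and 74% with 2, 3 and 4. With a coach level in the model, the rate is 4.2% to 5.8% for 2 to 4 coaches at ICCs of 0.02 to 0.10.

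**Step 4: the pooled change.** With 2 coaches and ICC 0.05, the standard error of the overall mean was 0.0352 across simulated datasets, against 0.0360 from the model with site only. The pooled estimate is essentially unharmed.

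**The case against.** Several points can fairly be made for the plan.

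- **No formal test of site variance is stated.** Site enters as clustering to be accounted for, and most of the planned contrasts are between kinds of client. This stands. The rejection rates show how far apparent site differences could mislead; they are not error rates of a planned test. The planned comparison by municipality and between sites still relies on the same understated standard error.
- **The size is assumed.** This stands too. The Strengths and Limitations section reports staff turnover, so the number of coaches a site uses over the years may exceed 2 to 4, and the effect shrinks as coaches increase.
- **Coach performance is measured separately**, through competency coding, checklists, surveys and interviews. These data may reveal a coach problem, but the stated analysis of fidelity is descriptive and does not enter the effectiveness models.
- **A condensed article may leave random-effect detail to an analysis plan that is not shown.** Such a plan may include a coach level. The point here concerns the levels that the article does name.

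A reader might also take the Introduction's aim to "understand how community-, organization-, provider-, and client-level factors contribute to implementation outcomes" as a promise to split effectiveness into provider and organization parts. It is not one: that sentence is about implementation outcomes and belongs to the general rationale.

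**Conclusion.** The point holds in a limited form. The stated models omit the unit that delivers the intervention, and a model with coach within site would serve the planned between-site and municipality comparisons better. Without it, about 1/J of any coach variance would be read as site variance and those comparisons would be overprecise. At a coach ICC of 0.05 the factor is about 1.31 with 2 coaches and 1.15 with 4. A 5% test of site differences with no true site variance would reject in about 82% down to 17% of datasets with 2 to 8 coaches, or about 33% down to 9% at an ICC of 0.02. All of this depends on an ICC and coach numbers that the article does not give.

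Stronger readings are not supported. A reader might infer that coach differences will be reported wholesale as site differences. With two or more coaches per site, half or more of the coach variance goes to the client residual. Only with one coach per site does all of it go to site, and there a coach term cannot separate the two. A reader might also infer that the main effectiveness result is compromised; the pooled change is essentially unaffected. Nothing here shows harm to the HbA1c logistic model, whose levels are not named.

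**What to change.** Store the ID of the delivering coach on each client record, using the majority coach if a client saw more than one. Add a random effect for coach within site to the hierarchical effectiveness models. Report client, coach and site variance separately. Keep single-coach sites in the model, and interpret their site effect as coach and site combined.

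The cost is one more variance term, which may be imprecisely estimated where sites have few coaches, and a data linkage. No new data collection is needed. Coaches already supply the session checklists (Table 1), and the coach surveys at 5, 10 and 20 clients (Table 2) already require a count of clients per coach.

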### Organization Implementation Sites

Eleven distinct regional YMCAs across 8 provinces in Canada will participate in this study (see Figure 3 for specific locations). In year 2, SSBC will be delivered in 11 initial implementation sites, one in each distinct YMCA region. Sites were purposively selected to maximize ethnocultural, population density, and socioeconomic diversity, as these contextual factors may influence implementation, effectiveness, and sustainability. Specifically, each site represents a region with high prediabetes prevalence, access to priority populations (operationalized in this project as health equity-owed groups who may face systemic barriers to access, opportunities, and resources to DPPs due to factors such as race, ethnicity, gender, and socioeconomic status; [11-16]), and staffing capacity to deliver SSBC within the organization. Each regional YMCA oversees several health and fitness facility buildings (often in distinct cities) into which SSBC delivery will scale up in years 3 and 4, for a total of 44 Canadian implementation sites.

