## Results

Program implementation within each region is occurring in a phased approach, with partners beginning program delivery in 1 site (2024-2025) before expanding to any additional locations (2025-2027). Program enrollment occurs continuously during the implementation phase across all sites. From May 2024 to November 2025, a total of 13 delivery sites began program delivery (1 regional YMCA decided to launch in 3 sites at once), 722 participants have enrolled in the program, and 406 have begun the program (153/342, 44.7% non-Western or Eastern European, 17/342, 5% of whom report identifying as Indigenous; 80/345, 23.2% men or 82/347, 23.6% male). Further, 334 participants have expressed interest in the substudy, of which 89 have had their first blood draw (19/89, 21.8% identify as a visible minority; 4/89, 5.3% indigenous; 16/82, 19.5% men or 16/81, 19.8% male). An additional 13 sites have confirmed they will launch the program in 2026.

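### Sex, gender and ethnicity covariates are given the job of handling correlation, which they cannot do, while the declared question of differential effectiveness is given no interaction test and sex and gender are listed together

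*Protocol article*

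**What the plan says.** Under Objective 2b, the protocol article first says that hierarchical multivariable regression will be used, "adjusting for potential confounders and accounting for within-subject and within-site clustering". The next sentence reads: "Covariates (ie, sex, gender, and ethnicity) will be included to adjust for within-subject and within-site correlations". No other purpose is given for these covariates, and nothing says whether sex and gender are alternatives or enter one model.

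The same paragraph sets out to evaluate the differential impact of the program. It then states: "Data will be disaggregated to examine differences in effectiveness by ethnicity, socioeconomic status, municipality, sex, and gender within and between sites". A further model is planned for HbA1c response at 24 months: "For the subsample, a multilevel binary logistic regression will be used to examine differences in sociodemographic factors". The cohort for this is described as follows: "a prospective cohort subsample of clients (n=1285) will be followed across 24 months".

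The Results section gives the sex and gender margins so far. Among clients who began the program they are "80/345, 23.2% men or 82/347, 23.6% male". In the substudy they are "16/82, 19.5% men or 16/81, 19.8% male". No sex-by-gender cross-tabulation is reported.

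**The concern.** Three things in this paragraph do not fit together.

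- **Purpose of the covariates.** Correlation within a client or a site is handled by random effects, a covariance structure, GEE or cluster-robust variance. A covariate that is fixed for the client shifts the expected value and may explain a little between-client variance, but it does not do that job. With two sentences assigning the same task to different terms, an analyst cannot tell which terms carry the clustering or what the covariates are for.
- **The equity question.** There is no comparator, so effectiveness is change from baseline. Whether change differs by sex, gender or ethnicity is a question about characteristic-by-time terms. The only role written down for the covariates does not address it, and separate subgroup results side by side do not test a difference.
- **Sex and gender together.** If the two variables agree for nearly every client and both enter one model, their separate coefficients rest on the few discordant clients.

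At stake are the sex-, gender- and ethnicity-specific conclusions, which are a declared aim. The overall change estimate is not at risk.

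**Working it through.** The protocol article states no figure on this point that needs reproducing, apart from the percentages checked in step 3.

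**1. Do the covariates remove the correlation?** This was checked by 300 simulated trials of 44 sites (the protocol's planned total) with 29 clients each (44 × 29 = 1276, close to the 1285 in the subsample) and 3 visits. Assumed variance shares were site 0.05, client 0.55 and residual 0.40. Assumed effects were 0.2 for sex and 0.2 for ethnicity, with gender discordant from sex in 2% of clients. Mean ICCs before and after regressing on sex, gender and ethnicity:

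| | Before | After |
|---|---|---|
| Within-subject ICC | 0.61 | 0.60 |
| Site ICC | 0.05 | 0.05 |

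The correlation is still there after adjustment.

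**2. Do main effects address differential change?** Write the linear mixed model for client i in site j at time t as

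Y = β0 + β(t) + αX + u(j) + b(ij) + e(ijt), with β(0) = 0 and X fixed over time.

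Change from baseline is Y(t) − Y(0) = β(t) + e(t) − e(0). The term αX cancels. With complete visits the estimated change is the same with or without X, and it is forced to be equal in all groups. With missing visits it moves a little. Adding δX at times after baseline gives a change of β(t) + δX, and δ is then the difference in effectiveness that the aim asks about.

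**3. How collinear are sex and gender?** The reported percentages reproduce: 80/345 = 23.19%, 82/347 = 23.63%, 16/82 = 19.51%, 16/81 = 19.75%.

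Take p = 80/345, q = 82/347, both coded in two categories, and s = √[p(1−p)q(1−q)] = 0.179. The margins alone allow phi from −0.31 to 0.99. They are compatible with near-identity but do not establish it.

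For an assumed discordant proportion d, the joint proportion is p11 = (p + q − d)/2, phi = (p11 − pq)/s, VIF = 1/(1 − phi²), and the standard error factor is √VIF. For d = 0.02: p11 = (0.2319 + 0.2363 − 0.02)/2 = 0.2241, phi = (0.2241 − 0.0548)/0.1793 = 0.944, VIF = 9.2, factor = 3.0.

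| Assumed discordance | phi | VIF | SE factor | Discordant among 1285 |
|---|---|---|---|---|
| 0.5% | 0.99 | 36 | 6.0 | about 6 |
| 1% | 0.97 | 18 | 4.3 | about 13 |
| 2% | 0.94 | 9.2 | 3.0 | about 26 |
| 5% | 0.86 | 3.9 | 2.0 | about 64 |
| 10% | 0.72 | 2.1 | 1.4 | about 129 |

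These factors are for a linear model with the two variables fitted jointly, ignoring other covariates. They are a guide only for the logistic model.

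**The case against.** The strongest reply is that the defect is one badly worded sentence. A reader who sees only that sentence might infer that clustering goes unmodelled. The documents do not support this: the sentence before it assigns clustering to hierarchical models, and the subsample regression is multilevel. That part of the reply stands in full.

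A reader might also infer that the data show sex and gender to be practically one variable. They do not. Two margins are not a cross-tabulation, and the denominators differ (345 and 347), so the margins do not even fix a minimum number of discordant clients. The two extra respondents on sex could be males who left the gender item blank. Nor does collinearity between adjustment covariates bias the overall change, and disaggregating by each variable in turn does not require both in one model. This limits the point to separate coefficients read from a joint fit.

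On interactions, it can fairly be said that nothing restricts the covariates to main effects, that an article may leave such detail to the full plan, and that the subsample logistic regression does compare groups directly. The last of these stands for dichotomised HbA1c response. It does not cover the other outcomes or HbA1c change itself, and the one role that the article does give the covariates is the wrong one.

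Finally, a reader might infer that a coach level is missing and that standard errors are therefore too small. The article does not say that one coach sees a client throughout, and it gives no coach ICC or caseload. Coach and region terms are also detail that an article may leave out.

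**Conclusion.** The stated purpose of the covariates is wrong as written. That conclusion rests on how such models work, not on the assumed simulation values. Correcting it alone changes no result, because the hierarchical structure already carries the clustering.

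The substantive gain is in the equity aim. Time-fixed main effects leave the estimated change essentially unaltered and cannot show differential change, and disaggregation alone does not test it. An explicit interaction with time would.

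The sex and gender point is conditional. If both are fitted together, for example in the subsample logistic regression, and discordance is about 2% or less, their separate standard errors rise roughly 3-fold or more. At 5% the factor is 2.0, and at 10% it is 1.4. The sponsor holds the cross-tabulation and can settle which case applies. No planned estimate of overall change is shown to be invalid.

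**What to change.** Replace the covariate sentence under Objective 2b with:

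> Within-subject and within-site correlation is modelled by random effects for client and site. Sex or gender (in separate models, or as one combined variable) and ethnicity are included as adjustment covariates, and differences in effectiveness are tested by characteristic-by-time interactions, reported alongside the disaggregated results.

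State in the same place whether sex and gender both enter the subsample logistic regression, and report their cross-tabulation. A coach-level random effect is optional; the documents do not show that it is needed.

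The cost is a wording change and slightly more analysis work, with no new data collection. Interaction estimates for small subgroups will have wide intervals, and these should be reported as such.

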#### Recruitment and Consent

##### SSBC Clients

Recruitment strategies will vary across delivery sites, based on the local connections previously or newly established by the research team and delivery team. A series of generic recruitment materials (eg, posters, pamphlets, or social media posts) and potential recruitment pathways (eg, health assessment days and physician referrals) have been generated by the research team and will be shared with all delivery sites. These recruitment strategies will be included in the implementation strategies’ blueprint and toolkit. Each site will tailor their recruitment plan to the local contextual needs with support from the research team.

Interested or referred individuals will complete an eligibility survey to determine their eligibility for SSBC. Individuals are eligible for SSBC if they are 18 years of age or older, able to read and speak English, and meet one of the following criteria: (1) have been diagnosed with prediabetes by a physician, (2) have an HbA_1c_ of 5.7%-6.4%, (3) have an American Diabetes Association risk assessment score indicating high risk (≥5), or (4) have achieved T2D remission (have an HbA_1c_ of <6.5%) without any diabetes-related medications for a minimum of 3 months. Eligible individuals will be directed to an online consent form. Following completion, individuals will be scheduled for their first SSBC session at their local YMCA implementation site.

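### The only covariates named for the effectiveness models are sex, gender and ethnicity, so differences in who was recruited may be read as differences in how well SSBC works across sites and groups

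*Protocol article*

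**What the plan says.** Objective 2b plans hierarchical multivariable regression for the effectiveness outcomes, "adjusting for potential confounders and accounting for within-subject and within-site clustering". The next sentence gives the covariates: "Covariates (ie, sex, gender, and ethnicity) will be included to adjust for within-subject and within-site correlations".

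The comparisons of interest follow in the same paragraph: "Data will be disaggregated to examine differences in effectiveness by ethnicity, socioeconomic status, municipality, sex, and gender within and between sites". For the HbA1c subsample (n=1285), a multilevel logistic model at 24 months then compares sociodemographic factors between clients with and without a clinically significant fall in HbA1c. That sentence names neither baseline HbA1c nor the route of entry.

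Under Recruitment and Consent (SSBC Clients), an adult who reads and speaks English qualifies by meeting any one of four criteria: a physician's diagnosis of prediabetes, HbA1c 5.7%-6.4%, a high American Diabetes Association risk score (≥5), or T2D remission off diabetes medication. On recruitment the section says "Recruitment strategies will vary across delivery sites, based on the local connections previously or newly established by the research team and delivery team" and "Each site will tailor their recruitment plan to the local contextual needs with support from the research team". The shared materials include "potential recruitment pathways (eg, health assessment days and physician referrals) have been generated by the research team and will be shared with all delivery sites".

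Table 3 lists age and "Prediabetes diagnosis or ADA^b^ diabetes risk score" at intake, and laboratory HbA1c at baseline for the subsample.

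**The concern.** The sentence that should carry out the promise of confounder adjustment does two things badly.

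- **Wrong purpose.** It assigns the three covariates to within-subject and within-site correlation. A covariate may explain part of the variance between sites, but the correlation that remains is handled by random effects or a covariance structure. Covariates belong to the confounding problem.
- **Poor fit to the contrasts.** For ethnicity, sex and gender, the named covariates are largely the contrasts themselves. For sites and municipalities, nothing on the list describes glycaemic status at entry.

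This matters because the entry criteria admit clients with different starting glycaemia. A client admitted on risk score alone needs no glycaemic test and may have a normal HbA1c, with less room to fall. A site that relies on health assessment days could admit more such clients than one that relies on physician referral. Its mean change would then look smaller even if SSBC worked equally well for clients with the same starting risk.

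The responder model is exposed in the same way. A sociodemographic group with more low-baseline clients may appear not to respond.

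The stakes are practical. There is no comparison group, the subsample is meant to show differential impact, and under Objective 3a the data from Objectives 1 and 2 feed reports to each YMCA that inform whether and how SSBC continues.

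**Working it through.** No figure in the article is in dispute. It gives no effect size, SD, intraclass correlation or power, so n=1285 cannot be reproduced, and the point does not depend on it. The check compares the text and then illustrates the size with assumed inputs.

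**1. The text side by side**

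| Element | What the article gives |
|---|---|
| Promise | Adjustment for potential confounders, none named in that sentence |
| Named covariates | Sex, gender, ethnicity, closed by ie |
| Purpose given | Within-subject and within-site correlation |
| Contrasts planned | Ethnicity, socioeconomic status, municipality, sex, gender, within and between sites |
| Could differ between those contrasts | Age, entry criterion, socioeconomic status, starting HbA1c; none is named as a covariate |

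**2. Group contrast, assumed inputs**

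Assume that risk-score entrants start 0.40 HbA1c points lower than the others (5.55% against 5.95%), that the fall shrinks by 0.25 points per 1% of lower baseline, and that there is no true group difference.

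Spurious difference = slope × baseline gap × difference in risk-score share

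- 10-point difference in share: 0.25 × 0.40 × 0.10 = 0.01
- 20-point difference: 0.25 × 0.40 × 0.20 = 0.02
- 30-point difference: 0.25 × 0.40 × 0.30 = 0.03

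Simulation with 44 sites of 29 clients (1285/44 = 29.2) agreed: 0.010, 0.020 and 0.030. Adding route and baseline brought the difference to 0.000. Comparing groups within sites does not remove the bias: with a 20-point difference it stayed at 0.018 to 0.020 points. It was then nominally significant in 13% to 27% of simulated studies, depending on the assumed residual SD.

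**3. Site contrast, separate assumed inputs**

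Let p1 and p2 be the shares of clients at two sites who enter on a glycaemic criterion. Let dA and dB be the mean changes for glycaemic and risk-score entrants, equal at both sites.

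Spurious site difference = (p1 − p2) × (dA − dB)

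- Low: (0.60 − 0.40) × (−0.10 + 0.05) = −0.01
- Central: (0.70 − 0.30) × (−0.15 − 0.00) = −0.06
- High: (0.80 − 0.20) × (−0.30 − 0.00) = −0.18

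In 1000 simulated comparisons of the central case (SD of change 0.30), a model with sex and ethnicity left the whole −0.06. It reached p<0.05 in 11% of runs at 29 clients per site and 34% at 117 per region (1285/11 = 116.8). With entry route added, the difference was about 0.00 and rejection was 5% to 6%.

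**The case against.** The strongest reply is that the article does promise adjustment for potential confounders, and that a condensed article may leave the full list to an analysis plan not shown here. That stands against one tempting reading: that the plan adjusts for sex, gender and ethnicity and nothing else. The document does not support it. What it supports is that the only list printed is closed, does not match the promise, and carries the wrong purpose.

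Four further points stand, in whole or in part.

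- **Route mix is inferred.** The four criteria are the same at every site; only recruitment varies. A different mix by site is plausible but not stated, and nothing in the article links entry route to ethnicity.
- **Baseline values are not ignored.** In a repeated-measures model they enter as outcome data. Conditioning on baseline when groups were not randomised is a debatable choice that changes the question, so it should not be required in every comparison. The responder model is different: its outcome is a fall from baseline, so the starting value directly limits who can meet it.
- **Disaggregation can be descriptive.** This is partly right, but the article also states an aim of assessing differential impact and plans regression for it.
- **Entry data are coarse in print.** Table 3 combines diagnosis and risk score in one row, has no row for remission, and schedules laboratory HbA1c in the subsample only. The criteria overlap. The eligibility survey must nevertheless establish that a criterion was met, so the information should be recoverable.

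Covariate-by-time terms, time since site launch and standardisation belong to an analysis plan, and their absence is not part of this point.

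**Conclusion.** The point holds as a conflict within the printed text. The covariate sentence is narrower than the promise before it, gives covariates a task that belongs to the random effects, and omits the variables most likely to separate who was recruited from how well SSBC works. Differences in case mix may therefore be read as differences in effectiveness. It is not established that they will be.

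The size is illustrative only. Under the assumptions for the group contrast the spurious difference is about 0.01 to 0.03 HbA1c points. For two sites with more sharply different route mixes, the separate assumptions give 0.01 to 0.18. A reader might infer a larger group effect: about 0.027 points at a 20-point difference in share is possible. That requires a strong site-level correlation between minority share and risk-score share, for which the article gives no basis. The reasoning about the logistic model is qualitative, since the article does not define the threshold for a clinically significant reduction.

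**What to change.** 1. State that random effects (or a covariance structure) for client and site handle the clustering, and that covariates address confounding.
2. Replace the closed list, for the between-site and subgroup comparisons, with age, sex, gender, ethnicity, socioeconomic status (where the demographic items collect it) and entry criterion from the eligibility survey.
3. Add baseline HbA1c and entry criterion to the 24-month logistic model.
4. Report effectiveness by entry route. Show unadjusted differences beside the adjusted ones, because the adjusted ones answer a conditional question.

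The cost is a change of wording and a little more analysis. Age and, in the subsample, baseline HbA1c are already scheduled. A rule is needed for clients who meet more than one entry criterion, and it should be confirmed that the eligibility survey stores which criteria were met.
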